### Study visits

2.6

All patients are followed from day 0 through day +56 or death. The planned visits are: 1) randomization visit (day 0) in which the patient is screened and eventually included in the study; 2) Hospitalization visits that are variable according to the period of admission; 3) Visits on day +28 ± 3 and on day +56 ± 3 from randomization. These visits are face-to-face to evaluate whether patients present a relapse or worsening of the disease, as well as the presence of adverse events or mortality. Specific procedures that are performed on each visit are detailed in Table 1 and the *evaluation methods* section.

**Table 1 tbl1:** Flow-chart of the trial showing the procedures that will be conducted in each visit.

	Randomization visit (day 0)	Hospitalization visits (days n)	Visit 28 ± 3 days after the start of treatment	Visit 56 ± 3 days after the start of treatment
Inclusion/exclusion	x			
Informed consent	x			
Randomization	x			
Demographics Comorbidities	x			
COVID-19 clinical data	x			
Vital signs	x	x	x	x
8-point Ordinal scale	x	x	x	x
Analysis (Hematology, Chemistry, Coagulation)	x	x	x	x
Tacrolimus levels		x		
Cytokines	x	x	x	x
Viral load (blood)	x	x	x	x
Nasopharyngeal SARS-CoV-2 PCR	x		x	x
Clinical stability	x	x	x	x
Lung tests (x-ray, CT scan, chest US, 6MWT, functional tests)	x	x (1)	x (1)	x
Study treatment	x	x	x	x
Concomitant medication	x	x	x	x
AE registration	x	x	x	x

(1) according to the attending physician.

### Evaluation methods

2.7

#### Clinical parameters

2.7.1

The randomization visit (day 0) includes the collection of demographic variables [date of birth, sex, ethnicity], weight and height, clinical data [symptoms onset date, hospital admission date, clinical manifestations, radiological characteristics of pulmonary infiltrates], comorbidities [smoking and alcohol consumption, Charlson index], functional and cognitive assessment [Barthel and Pfeiffer index respectively], 8-point Ordinal scale (https://clinicaltrials.gov/ct2/show/NCT04280705), vital signs [temperature, blood pressure, heart rate, respiratory rate, oxygen assessment and supply (type of oxygen mask and FiO2, non-invasive or invasive ventilator support devices, or ECMO, PaO2/FiO2 and/or SatO2/FiO2), and conscious level using the Glasgow Coma Scale], as well as concomitant medication. With all these data we automatically calculate body mass index (BMI), the Pneumonia Severity Index (PSI) and CURB-65 index, and determine the extent of organ failure (SOFA score). The hospitalization visits include the collection of vital signs, 8-point Ordinal scale, adverse events and mortality. Visits on day +28 ± 3 and +56 ± 3 include vital signs, ordinal scale, relapse or worsening of the disease, adverse events and mortality.

#### Tests and other procedures

2.7.2

A blood analysis is performed before starting the study treatment with the following biomarkers: 1) hematology (hemoglobin, hematocrit, platelet count, absolute lymphocyte count, leukocyte count with differential) assessed using Sysmex® XN2000 analyzer (Sysmex Europe GmbH; Norderstedt; Germany); 2) basic chemistry (creatinine, albumin, ALT, total bilirubin) and inflammatory parameters (ferritin, D-dimer, CRP, LDH) measured with Cobas® 6000/8000 analyzer (Roche Diagnostics®, Risch-Rotkreuz, Switzerland), which has spectrophotometry and immunochemistry modules with electrochemiluminescent detection; and 3) coagulation (activated partial thromboplastin time, prothrombin time and fibrinogen) using ACLTOP® 550 analyzer (Werfen®; Barcelona, Spain). Furthermore, all patient samples are collected, processed and stored at randomization, and weekly after randomization by the BUH-IDIBELL Biobank following standard operating procedures. During hospitalization, a blood analysis is performed 3 times a week with the same parameters as used at randomization. Tacrolimus levels are measured using a method based on ultra-high-performance liquid chromatography coupled with tandem mass spectrometry (HPLC-MS/MS) [18].

The QTc interval is evaluated using an ECG before randomization, and an electrocardiogram 3 times a week is recommended during hospitalizations. All pulmonary tests performed during hospitalization at the discretion of the treating physician are being collected (chest x-Ray CT scan). A chest CT scan, the 6-min walk test (6MWT) and functional respiratory tests on day +56 ± 3 follow-up visit are performed.

In addition, a follow-up oropharyngeal SARS-CoV-2 RT-PCR is performed on day +28 ± 3 and +56 ± 3 visits. Blood viral load will be evaluated using quantitative RT-PCR to assess the impact of immunosuppressive treatment on viral dynamics. Microbiological tests are being carried out by the Microbiology Department at the BUH.

All samples will be sent to the Immunology Laboratory of the Biomedical Diagnostic Center at the Clinic Hospital in Barcelona to perform a multiple cytokines quantification technique by Luminex®. Concentration of the following cytokines will be analysed: IL-6, IL-18, CXCL10, CXCL9, TNF-alpha, IFN-alpha, IFN-beta, IFN-gamma, IL1RA, IL1-beta, IL10 and IL-2R/CD25.

### Outcomes

2.8

#### Primary end point

2.8.1

Average of days until *clinical stability* from treatment randomization.

Treatment failure is defined as: 1) patient who does not meet the criteria for clinical stability 56 days after starting treatment; 2) patient presenting with a grade 3 or 4 adverse event attributed to trial treatment; or 3) patient who dies after being included in the clinical trial.

#### Secondary endpoints

2.8.2

-Days until normalization of each of the clinical parameters (body temperature, PaO2/FiO2 and/or SatO2/FiO2, respiratory rate) from day +1 through day +56.-Days until normalization of each of the analytic parameters (D-dimer, CRP, ferritin, LDH, IL-6) from day +1 through day +56.-Number of patients requiring non-invasive and invasive ventilatory support devices during hospitalization.-Clinical status according to the 8-point Ordinal scale from day +1 through day +56.-Number of patients who reach a clinical status ≤2 after 10 days or hospital discharge, whichever is first.-Number of patients who reach clinical stability after 10 days or hospital discharge, whichever is first.-Value of each of the analytical values (D-dimer, CRP, ferritin, LDH, IL-6) after 10 days or hospital discharge, whichever is first.-Days with trial experimental treatment.-Days until hospital discharge.-Changes in blood quantitative viral load by RT-PCR before start treatment and weekly during hospitalization.-Changes in expanded cytokine profile before starting treatment and weekly during hospitalization.-Long-term efficacy (28 and 56 days after trial treatment initiation) measuring whether clinical stability are maintained and the incidence of relapse of COVID-19 illness.-Description of the radiological abnormalities (chest x-ray, chest CT scan, functional tests) at day 56.-Adverse events according to their severity and relationship to trial experimental treatment.-COVID-19 related mortality at day +28 and + 56 after randomization.-All-cause mortality at day +28 and + 56 after randomization.

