#### Statistical considerations

2.9.2

A descriptive analysis of the study variables will be carried out. Continuous variables will be described as mean and Standard Deviation (SD) or as median and range; and categorical variables as absolute frequencies and percentages. The main analysis will be performed when all patients reach clinical stability or failure. If patients are in hospital for 56 days, they will be considered clinical failures. Comparison between average time to achieve clinical stability between the two study groups will be measured using the log-rank test. To quantify the degree of association, hazard ratio will be estimated with a Cox proportional hazards model using a 95% confidence interval.

Efficacy analyses will be performed for the intention to-treat (ITT) population. If a proportion of subjects >10% is detected to have relevant deviations from the protocol (for example, non-compliance with the selection criteria, non-compliance or inability to receive the trial treatment), the per protocol (PP) analysis will exclude those subjects with such deviations. If this group is defined, all exploratory efficacy analyses will be repeated as a sensitivity test.

As additional analysis, a Cox proportional hazards model, adjusted for clinically relevant confounding factors such as age, sex, comorbidities using the Charlson index, indexes to assess the severity of pneumonia (PSI and CURB-65), index of organic dysfunction (SOFA) and inflammatory parameters will be performed. In addition, prespecified subgroup analyses involving sensitivity analysis will be used to evaluate outcomes in patients not receiving invasive mechanical ventilation.

For evaluation of secondary variables, we will calculate unadjusted and adjusted estimations of effect size and the corresponding 95% confidence intervals using linear, logistic or proportional hazards Cox regression. Study adverse events will be described according to their severity and relationship with other treatments, and will be compared between treatment groups. Midway through recruitment, i.e. 21 patients per arm, an intermediate efficacy and safety analysis will be performed. For this, a correction of the type I error will be applied following Lan-DeMets (O'Brien – Fleming) in evaluation of efficacy.

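### Days to normalisation of laboratory markers run to day 56, but blood sampling thins out at discharge; analysed by ordinary Cox or linear regression, the arm discharged earlier can be recorded as normalising later

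*Protocol article*

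**What the plan says.** All references are to the protocol article.

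- **Endpoint** (2.8.2, Secondary endpoints): "Days until normalization of each of the analytic parameters (D-dimer, CRP, ferritin, LDH, IL-6) from day +1 through day +56".
- **Sampling in hospital** (2.7.2, Tests and other procedures): "During hospitalization, a blood analysis is performed 3 times a week with the same parameters as used at randomization". The listed panel has "inflammatory parameters (ferritin, D-dimer, CRP, LDH) measured with Cobas® 6000/8000 analyzer". IL-6 is not in that list. It is named in the Luminex cytokine set in the same section.
- **Cytokine timing** (2.8.2): "Changes in expanded cytokine profile before starting treatment and weekly during hospitalization".
- **Visits** (2.6, Study visits, and Table 1): "Hospitalization visits that are variable according to the period of admission", followed by "Visits on day +28 ± 3 and on day +56 ± 3 from randomization". Table 1 has no other column after discharge.
- **Analysis** (2.9.2, Statistical considerations): effect sizes for secondary variables are estimated "using linear, logistic or proportional hazards Cox regression".

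The article gives no rule for a marker that is still abnormal at the last in-hospital sample, and names no method for interval-censored data.

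**The concern.** The gap between samples is two to three days in hospital and can be several weeks after discharge. Time to discharge is itself a secondary efficacy endpoint, and the treatment is expected to speed recovery. The definition of clinical stability in 2.5 contains no laboratory marker, so nothing in the article ties going home to normal ferritin, D-dimer, CRP or LDH. Sampling is therefore likely to be sparser in the arm that recovers sooner.

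For a patient discharged while still abnormal, the date of the first normal sample is set by the visit calendar and not by the biology. If that date enters a Cox or linear model as an exact time, a true benefit on the markers can be hidden, and no effect can look like harm. These markers carry much of the trial's anti-inflammatory rationale, so such a result would be read with interest.

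**Working it through.** **The plan's own figure.** The article gives no number for this endpoint. Its sample size does reproduce: Freedman events = ((1 + 0.52)/(1 − 0.52))² × (1.960 + 0.842)² = 10.03 × 7.85 = 78.7, so 79; 79/0.95 = 83.2, so 84 patients, 42 per group. The point does not depend on this. Only the control median (16 days) and the hazard ratio (0.52) are reused below.

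**One patient.** Suppose ferritin truly normalises on day 13.
- Discharged on day 9: the next scheduled sample is day 28, so the recorded time is 28 days, 15 days late (12 to 18 days late with the ±3-day window).
- In hospital to day 18, sampled every 7/3 days: the next sample is at 6 × 7/3 = 14 days, so the recorded time is 1 day late.

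**How many patients are affected.** As a stand-in for length of stay, take exponential times with median 16 days (control) and 16 × 0.52 = 8.3 days (experimental). With exponential normalisation of median m in both arms, independent of stay, the share discharged before normalisation is m/(m + median stay). For m = 10:
- control: 10/26 = 38%
- experimental: 10/18.3 = 55%

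The simulation, which sets a minimum stay of 3 days, gives 37% and 52%.

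**Effect on the test when the marker effect is nil.** 42 per arm, 500 runs per row, two-sided log-rank test at 5%, event dated by the first sample at or after true normalisation. HR is experimental versus control for normalising, so a value below 1 means recorded as slower on treatment.

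| True median, both arms (days) | Correlation of stay and normalisation | Three times weekly: HR, rejection | Weekly: HR, rejection |
|---|---|---|---|
| 6 | 0 | 0.75, 14.8% | 0.58, 35.4% |
| 6 | 0.6 | 0.69, 29.2% | 0.53, 43.2% |
| 10 | 0 | 0.78, 12.6% | 0.71, 15.4% |
| 10 | 0.6 | 0.71, 20.8% | 0.59, 37.2% |
| 14 | 0 | 0.82, 8.4% | 0.79, 12.2% |
| 14 | 0.6 | 0.73, 18.0% | 0.71, 17.0% |
| 20 | 0 | 0.86, 6.8% | 0.86, 9.2% |
| 20 | 0.6 | 0.82, 11.6% | 0.83, 10.6% |

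Control run with equal stays (median 16 days in both arms, true median 14, correlation 0.6): HR 1.00, rejection 5.2%. The difference in discharge times is what produces the bias.

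**Does a different analysis remove it?** A second set of runs uses log-normal normalisation times (SD 0.6 on the log scale), 40 per arm, discharge 2 days after stability, and three-times-weekly sampling.

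| Analysis | No effect (14 v 14 days): runs favouring control, nominal 2.5% | Benefit (14 v 10 days): power |
|---|---|---|
| First normal sample as exact date | 24% (correlation 0), 43% (0.6) | 5% |
| Interval-censored model | 3% (0), 7% (0.6) | 62% (0), 49% (0.6) |
| Normalisation fully observed | – | 65.7% (0), 61.3% (0.6) |
| Ordinary log-rank, censored at discharge | 1.8% (0), 13% (0.6) | 45% (0) |

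Interval censoring recovers most of the lost power and nearly restores the error rate. Some bias remains at the higher correlation.

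**The case against.** **The dating rule is not stated.** The article does not say that the first normal sample dates the event, and rules on event dates and censoring usually sit in the analysis plan, which is not shown. This stands, so the point is conditional on that dating. But the sampling gap is fixed by the design, the methods the article names do not deal with it, and no analysis plan can create samples between discharge and day 28. Censoring at discharge works if discharge and normalisation are independent. It does not fully work if they are related, which is likely because both follow recovery.

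**Not every early discharge delays the record.** A reader might infer that earlier discharge always means later recorded normalisation. The documents do not support that. A marker seen to normalise in hospital is dated to within 2–3 days, and only patients discharged before that are affected.

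**The size is assumed.** The article gives no length of stay, marker times or discharge rule. The direction was the same in every scenario with earlier discharge on treatment, but no single false-positive rate can be defended.

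**IL-6.** A reader might conclude that IL-6 is certainly measured only weekly and that its day 10 value has no sample. That goes too far. Weekly-only measurement is inferred from its absence from the routine list, while 2.8.2 groups it with the routine markers. The value endpoint is taken at day 10 or at discharge if sooner, not at day 10 alone. The Biobank sentence in 2.7.2 gives weekly storage without an explicit end at discharge, but the cytokine endpoint limits it to the hospital stay and Table 1 shows no visit before day 28.

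**Importance.** This is one of many secondary endpoints in a phase II trial, and the companion endpoint (marker value at day 10 or discharge) avoids the gap. Both are true and limit the weight of the point.

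**Conclusion.** The concern holds in a limited form. For D-dimer, CRP, ferritin and LDH, the endpoint asks for a time that the schedule cannot observe once a patient leaves hospital with the marker still abnormal. If first normal samples are treated as exact dates in the regressions the article names, the comparison is biased against the arm discharged earlier, and so against an effective treatment.

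With no true marker effect, the illustrative false-positive rate ranges from about 7% to 43% across the assumptions used: median stays of 16 v 8.3 days, true marker medians of 6 to 20 days, correlation 0 or 0.6, and three-times-weekly or weekly sampling. If stays do not differ between arms, the bias disappears. The primary endpoint and the sample size are unaffected, and the documents do not show that the trial will report false harm. For IL-6 the problem is coarser if the weekly cytokine set is its only source, which the article should state.

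**What to change.** 1. Keep the endpoint. Among patients abnormal at day 0 for the marker in question, analyse time to normalisation as interval-censored between the last abnormal and the first normal sample (available in R, the software named in the article). Use actual sample dates, and right-censor patients never seen normal at their last sample.
2. State a rule for deaths before normalisation, for example counting them as not normalised through day 56.
3. Report the proportion normal at day 28 as a supportive summary only. Under the log-normal assumptions above its power is about 32% for 14 v 10 days, 6% for 10 v 7 and 0% for 6 v 4, because nearly everyone is normal by then when normalisation is quick.
4. Do not rely on censoring at discharge as the main remedy. Note in the report that interval censoring leaves a small bias if discharge and normalisation are strongly correlated.
5. State how often IL-6 is measured. Unless it is also in the routine bloods, analyse its time to normalisation as interval-censored on the weekly samples, and tie the IL-6 value at day 10 or discharge to the nearest scheduled weekly sample.

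Cost: no new samples and no endpoint removed, which fits the statement in 2.12.1 that earlier key outcomes are retained. Expect slightly wider intervals and a little more analysis work. The rule should be fixed before the data are compared by arm.

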#### Inclusion criteria

2.2.1

1)COVID-19 infection confirmed by nasopharyngeal RT-PCR,2)New pulmonary infiltrates (either by chest X-ray or computerized axial tomography),3)Respiratory failure (PaO2/FiO2 <300 or satO2/FiO2 <220),4)High analytical inflammatory parameters (CRP >100 mg/L, and/or D-Dimer >1000 μg/L and/or Ferritin >1000 μg/L).

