#### Exclusion criteria

2.2.2

1)Critically ill patients with life expectancy ≤24h,2)Glomerular filtration ≤30 mL/min/1.73 m^2^,3)Leukopenia ≤4000 cells/μL or other conditions that cause immunosuppression,4)Concomitant potentially serious infections,5)Contraindication for the use of corticosteroids or tacrolimus according to the Summary of Product Characteristics,6)Known hypersensitivity to any of the study drugs, their metabolites, or formulation excipient,7)Previous participation in a RCT in the last 3 months.

All patients (or a legal representative) have to provide informed consent (ICF) prior to initiation of the study procedures.

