### Randomization

2.4

On day 0, patients are centrally and randomly assigned using the RedCap computer platform that allows data collection and patient randomization. Patients are not stratified by baseline variables. Participants are randomized in a 1:1 ratio into one of two study groups: methylprednisolone pulses, tacrolimus and SoC, or SoC alone.

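### The ventilatory-support endpoint is not limited to new use, so support already in place at day 0 and continuing after randomisation is scored as an outcome

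*Protocol article*

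**What the plan says.** The endpoint, in the Secondary endpoints section, is "Number of patients requiring non-invasive and invasive ventilatory support devices during hospitalization". It does not restrict the count to new use, and it does not name the patients at risk. A neighbouring item states its window in full: "Clinical status according to the 8-point Ordinal scale from day +1 through day +56".

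Three other sections determine who can be on support when follow-up starts:

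- **Inclusion criteria** require "Respiratory failure (PaO2/FiO2 <300 or satO2/FiO2 <220". They set no upper limit on the level of support.
- **Exclusion criteria** deal with severity of illness mainly through "Critically ill patients with life expectancy ≤24h". Neither non-invasive nor invasive ventilation is a reason for exclusion.
- **Clinical parameters** lists, among the data for the randomisation visit, "type of oxygen mask and FiO2, non-invasive or invasive ventilator support devices, or ECMO".

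The Randomization section adds: "Patients are not stratified by baseline variables". Statistical considerations specifies intention-to-treat for the efficacy analyses. It also plans a subgroup of patients without invasive ventilation, but does not say at what time that status is taken.

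**The concern.** The endpoint is meant to show whether treatment keeps patients off ventilatory support. A patient already on a device at randomisation cannot show that. If the device is still in use after day 0, the patient meets the endpoint as worded, and would do so in either arm.

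Two things follow. When baseline support is balanced between arms, these patients add the same number of events to each side and pull the comparison toward no difference, which masks benefit and harm alike. When it is unbalanced by chance, which is easy with 42 per arm and no stratification, the imbalance passes directly into the outcome and can shift it in either direction.

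**Working it through.** **Inputs from the document.** There are 42 patients per arm and 84 in total, allocated 1:1, with a type I error of 0.05 (taken as two-sided). The sample size belongs to the primary endpoint and can be reproduced. Freedman's formula with a hazard ratio of 0.52 and 80% power gives (1.960 + 0.842)² × (1.52/0.48)² ≈ 78.7, so 79 events. Then 79/0.95 = 83.2, so 84 patients. This figure is not in dispute. The article gives no event risk, baseline share or power for the ventilatory-support endpoint.

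**Assumed inputs.**

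- b is the share of each arm on support at day 0 and counted for that reason.
- p is the risk of newly starting support among the remaining patients.
- Two pairs of p are used: 40% control with 15% experimental, and 40% with 20%.

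**Step 1: dilution.** The risk counted in an arm is b + (1 − b)p. The difference between arms is therefore (1 − b) × (p_control − p_experimental). This is algebra and does not depend on the values chosen, provided b is the same in both arms.

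For b = 20%:

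- 40% and 15%: the counted risks are 0.20 + 0.80 × 0.40 = 52% and 0.20 + 0.80 × 0.15 = 32%. The difference falls from 25 to 20 points. The risk ratio moves from 0.15/0.40 = 0.38 to 0.32/0.52 = 0.62.
- 40% and 20%: the counted risks are 52% and 36%. The difference falls from 20 to 16 points. The risk ratio moves from 0.50 to 0.69.

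**Step 2: power.** This uses the two-proportion normal approximation at two-sided 5%, with pooled variance under the null. The count as worded uses 42 per arm. The count of new starts uses 42(1 − b) per arm.

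| Assumed new-start risks | b | As worded | New starts among patients at risk |
|---|---|---|---|
| 40% and 15% | 10% | 58% | 69% |
| 40% and 15% | 20% | 46% | 64% |
| 40% and 15% | 30% | 36% | 58% |
| 40% and 20% | 10% | 40% | 47% |
| 40% and 20% | 20% | 31% | 43% |
| 40% and 20% | 30% | 25% | 38% |

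Counting new starts has the higher power in every row, despite its smaller denominator.

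**Step 3: chance imbalance.** The standard deviation of the between-arm difference in baseline support is √(2b(1 − b)/42). It is 6.5 points for b = 10%, 8.7 for 20% and 10.0 for 30%.

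**The case against.** Four objections carry weight.

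**Hospitalisation means the time after day 0.** A reader might infer that support used and stopped earlier in the same admission is also counted, since the admission date is collected separately ("symptoms onset date, hospital admission date, clinical manifestations"). The document does not support this. Study visits places the hospitalisation visits after the randomisation visit, and Tests and other procedures contrasts sampling before treatment with sampling during hospitalisation. The viral-load endpoint draws the same contrast. On this reading a patient who comes off a device before the first hospitalisation visit need not count either. The patient who stays on the device after day 0 still does.

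**The wording may mean two counts.** A reader might infer a single composite, in which a patient on non-invasive support at day 0 who is later intubated adds nothing. The text does not define a composite, and separate counts for non-invasive and invasive support are an equally natural reading. Either way, support continuing from day 0 is counted at its own level.

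**The missing start may be shorthand.** A reader might set this item against the rest of the list as a clear exception. That goes too far. Of the other 15 items, five start at day +1 or at randomisation, and several others also state no origin. The defect is the absence of a restriction to new use, which an agreed start date alone would not cure.

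**Few such patients may enter, and adjustment is planned.** The Treatment section stops experimental treatment when invasive ventilation or ECMO is required, which suggests that few invasively ventilated entrants were expected. They are nevertheless not excluded, and non-invasive support at entry is unrestricted. The planned adjusted estimates may absorb part of a chance imbalance in severity. However, the covariates named as examples do not include baseline support, and adjustment cannot make a continuing case informative.

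The full protocol is not shown and may say more. The article nevertheless gives a worded endpoint, and that wording scores continuing support as an outcome.

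**Conclusion.** The concern holds in this limited form: as worded, the endpoint counts support that was present at day 0 and continued after randomisation, in a trial whose eligibility admits such patients and whose day-0 record covers them. The direction, toward no effect, is certain when baseline support is balanced between arms. The size cannot be derived from the document. It depends on assumed risks, on the assumed share on support at day 0, and on those patients remaining on support long enough to be counted. If some come off at once, b is smaller and so is the dilution.

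The power figures are illustrations and should not be read as properties of this trial. Under the second pair of risks, power is low with either definition, so the wording is not the only limit on what this endpoint can show. It is one secondary endpoint; the primary endpoint and the 84 patients are untouched. The change is worth making because it is cheap.

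**What to change.** Define the endpoint as new start of support after randomisation through day 56, reported in two parts:

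- (a) invasive ventilation or ECMO, among patients on neither at day 0;
- (b) non-invasive or invasive support, among patients on neither at day 0.

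A patient on non-invasive support at day 0 then contributes to (a). State how death without support is handled, because it would otherwise count as a favourable non-event: either count it as an event or report the composite of support or death alongside. Tabulate day-0 support by arm.

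Both denominators are fixed by a baseline variable, so the comparison remains randomised. The cost is a change of wording and use of day-0 data already collected. The downside is a somewhat smaller denominator for each part: at b = 20%, 0.80 × 42 ≈ 34 per arm for (b). Patients excluded from a part still contribute to the ordinal-scale and mortality endpoints.

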In summary, the TACROVID trial assesses the combined use of tacrolimus and methylprednisolone, in addition to the standard of care in patients with severe COVID-19 illness. The aim is to evaluate both the beneficial effect of tacrolimus on controlling viral replication and, in combination with methylprednisolone pulses, modulating the host-immune inflammatory response triggered by the virus. In addition, potential adverse events related to this immunosuppressive therapy are carefully followed-up throughout the investigation. The results of the present trial might encourage further RCTs to assess the efficacy and safety of new antiviral and anti-inflammatory drugs regimens, in sequential combination, at earlier clinical stages of COVID-19.

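### The viral-load and cytokine change endpoints use inpatient samples only, although both assays are scheduled to day 56; if treatment speeds recovery, later inpatient comparisons contrast differently selected groups

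*Protocol article*

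**What the plan says.** Three parts of the protocol article describe the same blood samples differently.

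- **Endpoint definition (section 2.8.2).** Viral load is "Changes in blood quantitative viral load by RT-PCR before start treatment and weekly during hospitalization". The cytokine endpoint is "Changes in expanded cytokine profile before starting treatment and weekly during hospitalization". Both stop when the patient leaves hospital.
- **Sample handling (section 2.7.2).** Here "all patient samples are collected, processed and stored at randomization, and weekly after randomization", and no restriction to the hospital stay is stated.
- **Schedule (section 2.6 and Table 1).** The rows for blood viral load and for cytokines are each marked at day 0, the hospitalisation visits, day 28 and day 56. The last two are face-to-face visits: "Visits on day +28 ± 3 and on day +56 ± 3 from randomization".

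For secondary variables, section 2.9.2 plans unadjusted and adjusted estimates "using linear, logistic or proportional hazards Cox regression". It does not mention series that end with discharge or death. Time to discharge is itself a secondary endpoint in section 2.8.2. The Discussion gives as part of the trial's aim to evaluate "the beneficial effect of tacrolimus on controlling viral replication", and names baseline and weekly viral load among the reasons for the interim look at 21 patients per arm.

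**The concern.** Leaving hospital is a post-randomisation event, and the experimental treatment is intended to bring it forward. A marker endpoint that counts only samples from patients still admitted therefore conditions on something the treatment may change. Randomisation protects the comparison of all patients at day 14. It does not protect a comparison of those who happen still to be inpatients at day 14.

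At stake is how the virological and cytokine results are read. The Discussion notes earlier reports linking steroids with slower coronavirus elimination, so readers will look closely at viral load in the experimental arm. The two post-discharge visits in Table 1 would give values for discharged patients, but the endpoint wording leaves them out.

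**Working it through.** **Inputs.** Section 2.9.1 gives a control median time to stability of 16 days, a hazard ratio (control relative to experimental) of 0.52, 42 patients per arm, 80% power, type I error 0.05 and 5% withdrawal. The protocol gives no length of stay and no mortality figure.

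**Step 1: the plan's own sample size.** Freedman's formula, two-sided (sidedness is not stated, but two-sided reproduces the figure):

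events = (1.960 + 0.842)² × [(1 + 0.52)/(1 − 0.52)]² = 7.85 × 10.03 = 78.7, rounded up to 79.

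79/0.95 = 83.2, rounded up to 84, or 42 per arm. The stated figure reproduces, so the same inputs can be used for the next step.

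**Step 2: who would still be in hospital.** Assume exponential times and let clinical stability stand in for discharge. The experimental median is 16 × 0.52 = 8.32 days. The share remaining at day t with discharge lag L is

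S(t) = exp[−ln 2 × (t − L)/median].

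Example, day 14, no lag: control exp(−0.693 × 14/16) = 0.545, and 0.545 × 42 = 22.9. Experimental exp(−0.693 × 14/8.32) = 0.312, and 0.312 × 42 = 13.1.

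| Day | Control, no lag | Experimental, no lag | Control, 5-day lag (assumed) | Experimental, 5-day lag (assumed) |
|---|---|---|---|---|
| 7 | 73.8% (31.0) | 55.8% (23.4) | 91.7% (38.5) | 84.7% (35.6) |
| 14 | 54.5% (22.9) | 31.2% (13.1) | 67.7% (28.4) | 47.2% (19.8) |
| 21 | 40.3% (16.9) | 17.4% (7.3) | 50.0% (21.0) | 26.4% (11.1) |
| 28 | 29.7% (12.5) | 9.7% (4.1) | 36.9% (15.5) | 14.7% (6.2) |

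Numbers of patients out of 42 are in brackets. Deaths are not modelled. The arms are depleted at clearly different rates from day 14 under either lag. At day 7 the difference depends strongly on the lag.

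**Step 3: how different the remaining groups might be.** A simulation gave each patient a latent severity (standard normal) that slows recovery, with an assumed log-hazard slope of 0.5 or 1.0 per SD and no drug effect on the marker. Mean severity among experimental patients still admitted exceeded that among controls still admitted by 0.12 to 0.17 SD at day 7, 0.20 to 0.23 SD at day 14 and about 0.26 SD at day 21.

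This is a gap in assumed severity, not in change from baseline. If change in the marker correlated 0.3 to 0.5 with severity (assumed), the marker gap at days 14 to 21 would be about 0.3 × 0.20 = 0.06 SD to 0.5 × 0.26 = 0.13 SD. The standard error of a two-group difference at the no-lag numbers is √(1/23 + 1/13) = 0.35 SD at day 14 and √(1/17 + 1/7) = 0.45 SD at day 21.

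**The case against.** The strongest reply is that the protocol fixes a sampling window and a family of models, not a comparison of weekly inpatient means. A linear mixed model with baseline adjustment fits the wording of section 2.9.2, and the form of a longitudinal model is ordinarily settled in the SAP, which is not at hand. Adjusted estimates are already planned. A constant severity offset cancels in change from baseline, so bias arises only if severity affects the course of the marker. The mechanism also needs the drug to alter recovery or mortality. If it does neither, this selection creates no difference between arms. Finally, these are two of 16 listed secondary endpoints in a phase II trial of 84 patients.

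Most of this stands, and it limits what can be said about size. It does not remove the point about the window. The restriction to the hospital stay is written into both endpoint definitions, so an SAP that follows the protocol would inherit it, and no choice of model brings back samples that the endpoint excludes.

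A reader might go further and infer that the experimental patients still in hospital would be sicker, so that the analysis as written is biased against the drug and could pass for delayed viral clearance. The documents do not support that. They say nothing about severity among those remaining. The controls still admitted are a selected group too. Deaths could shift the selection either way, and the gaps in step 3 rest on assumed slopes and lie within one standard error.

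**Conclusion.** The concern holds in a limited form. The endpoint window in section 2.8.2 is narrower than the sampling in Table 1 and section 2.7.2, and it ties two endpoints to a post-randomisation event that the treatment is meant to influence. If the drug works as the design assumes, later inpatient-only comparisons would set groups of unequal size and different selection against each other: roughly 23 vs 13 at day 14 and 17 vs 7 at day 21 (control vs experimental), or 28 vs 20 and 21 vs 11 with a 5-day lag.

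Those counts rest on exponential times, on stability as a proxy for discharge and on no deaths. The direction and size of any bias in change from baseline cannot be obtained from the protocol. It would also be wrong to conclude that blood is taken only in hospital: the schedule says otherwise, which is why the remedy is cheap. The primary analysis is not affected.

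**What to change.** Reconcile section 2.8.2 with Table 1 and section 2.7.2:

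- Define both endpoints on all scheduled samples at fixed days from randomisation (day 0, the weekly samples, day 28 and day 56), whether or not the patient has been discharged.
- Analyse all randomised patients with a repeated-measures model adjusted for the baseline value. Name an early time point such as day 7 as the main contrast, since selection is least there. State how deaths are treated.
- Present later inpatient-only values as descriptive.

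The day 28 and day 56 assays are already scheduled, so this is a change of wording with slightly more analysis work. The downside is a missing-at-random assumption for weekly samples not taken after discharge: Table 1 lists no visit between the hospital stay and day 28, so some such samples may not exist. Joint modelling with time to discharge, or worst-rank scoring, could be added as sensitivity analyses, but the fix does not depend on them.
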